### 6.3 Statistical analyses

All variables will be checked for normality using the Shapiro-Wilk test. Independent samples t-tests or Mann–Whitney U-tests will then be conducted, as appropriate, to examine: (1) pre-test differences between groups and (2) pre-test differences between students who completed the study and those lost to follow-up. If variables significantly differ between groups, they will be appropriately adjusted in the main analyses. Descriptive statistics will be presented (mean and standard deviation) for each group separately.

Linear mixed models will be used to analyse the differential change between groups on all outcomes from pre-test to post-test, using pre-test data as the covariate. Linear mixed models will be used because these models are robust enough to withstand the biases from missing data. All analyses will be conducted using SPSS 28.0 (Chicago, IL, USA). The level of significance will be set at  $p < 0.05$ .

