#### 5. PARTICIPATING SITES

This study is being conducted in one state university (Universitas Pendidikan Indonesia) in Bandung, Indonesia. The physical education course is offered to first-year or second-year

students as a requirement or as an elective course. This university has seven faculties: 1) Faculty of Education; 2) Faculty of Science and Math Education; 3) Faculty of Social Science Education; 4) Faculty of Language, and Literature Education; 5) Faculty of Technology and Vocational Education; 6) Faculty of Sport and Health Education; and 7) Faculty of Arts and Design Education. Students from the Faculty of Sport and Health Education are not required to take a physical education course, while students from the Faculty of Art and Design are required to enrol in the physical education course. For students from the other five faculties, they are allowed to choose between the physical education course or a variety of Arts courses. This organisation will divide students into three groups which will be appropriate for this study: 1) students who are required to enrol in the physical education course; 2) students who choose to enrol in the physical education course; and 3) students who do not choose to enrol and participate in a physical education course.

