### 6.2 Sample size including power calculation

The sample size calculation is based on the difference in change in the primary outcome (physical activity) from pre- to post-intervention in both group (intervention and control group). Based on previous studies on technology-based physical activity interventions in university students, mean effect sizes of around  $d = 0.5$  are expected in analyses. To detect such intervention effects in two-sided significance testing ( $\alpha = .05$ ) with a power of 80%, a sample size of 128 participants is required. Taking into account an expected study drop-out of about 20%, 150 participants must be included in the study and participants response rate of about 50%, hence, 300 students (six classes of physical education course) will be invited.

Number of Participants

N=6 physical education course lecturers

(a) n=3 will be assigned to the intervention group,

(b) n=3 will be assigned to the control group.

n=300 students will be randomised 1:1 to either an intervention arm

(a) n=150 a technology-supported physical education course (intervention group)

(b) n=150 non-technology-supported physical education course (control group).

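### Section 6.3 lets pre-test significance tests between arms decide which extra covariates enter the main model; a short list should be fixed in advance instead

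*Protocol*

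**What the plan says.** Protocol Section 6.3 sets out two steps. First, after a normality check, "Independent samples t-tests or Mann–Whitney U-tests will then be conducted, as appropriate, to examine: (1) pre-test differences between groups". Second, "If variables significantly differ between groups, they will be appropriately adjusted in the main analyses". The threshold is the general one: "The level of significance will be set at" p < 0.05. No candidate variables are listed, and the form of the adjustment is left open.

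The same section specifies linear mixed models for all outcomes, "using pre-test data as the covariate". In its natural sense, this keeps each outcome's own pre-test score in its model whatever the screen shows.

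Three other places bear on the point:
- Section 3 (Rationale) presents knowledge as a main determinant of physical activity in students of this age, and motivation as a well-established correlate.
- Section 9.1 measures physical activity, knowledge and five BREQ-2 motivation subscales at pre-test.
- Section 6.1 assigns six lecturers at random, three per arm according to Section 6.2.

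**The concern.** The rule selects covariates on the wrong quantity. Adjustment improves precision when a covariate predicts the outcome, and the size of its difference between arms says nothing about that. A strong predictor that happens to be balanced stays out, and a variable unrelated to the outcome can enter. The adjusted effect and its interval then come from a model that is unknown until the arms have been compared.

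The screening tests also treat students as independent, although lecturers are the units assigned. If students of one lecturer resemble each other at pre-test, these tests reject too often, and the model changes more often than the nominal 5% suggests.

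At stake are a main analysis that cannot be reproduced from the protocol alone, and some precision given away. This is not a matter of detail left to a later plan: the protocol states the rule.

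**Working it through.** **1. The plan's own figure.** Section 6.2 assumes d = 0.5, alpha 0.05 and two-sided testing ("To detect such intervention effects in two-sided significance testing"), and concludes "with a power of 80%, a sample size of 128 participants is required". The exact two-sample t-test calculation gives 63.8 per arm, rounded up to 64, so 2 × 64 = 128. The figure reproduces, and it serves as the base below.

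**2. How often a predictor is left out.** With no true imbalance and valid tests, each variable is flagged 5% of the time. Pre-test knowledge, for example, would be left out of the physical activity model 95% of the time.

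**3. How often the model changes by chance.** Seven scores are measured at pre-test (1 activity + 1 knowledge + 5 motivation). For any one outcome its own pre-test score is already included, so at most six others can be added. If the tests were independent, the chance that at least one is flagged is 1 − 0.95^6 = 26%. Correlation among the five subscales lowers this figure, and clustering raises it.

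**4. Effect of lecturer assignment on the screen.** With m students per lecturer and intraclass correlation ICC, the approximate flag rate is 2 × [1 − Φ(1.96 / √(1 + (m − 1) × ICC))]. The protocol gives no ICC, so the values are assumed. Here m = 25 comes from 150/6 and m = 50 from 300/6.

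| ICC | m = 25 | m = 50 |
|---|---|---|
| 0 | 5% | 5% |
| 0.01 | 8% | 11% |
| 0.02 | 11% | 16% |
| 0.05 | 19% | 29% |
| 0.10 | 29% | 42% |

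A simulation with six lecturers agrees to within about one point: 10%, 18% and 30% at m = 25 for ICCs of 0.02, 0.05 and 0.10.

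**5. Precision under individual randomisation.** N = 128, d = 0.5, 8,000 simulated trials per row. Here r is the covariate's correlation with the outcome that remains after the outcome's pre-test value. The protocol gives none, so r is assumed.

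| r | Power, never adjust | Power, adjust if significant | Power, always adjust |
|---|---|---|---|
| 0.2 | 79.6% | 79.7% | 80.8% |
| 0.3 | 81.2% | 81.3% | 84.2% |
| 0.5 | 79.8% | 80.9% | 89.5% |

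The rule loses 1.1, 2.9 and 8.6 points against always adjusting. At r = 0.5 the standard deviation of the estimated effect is 0.177 without adjustment, 0.170 under the rule and 0.153 with fixed adjustment. As an analytic check, the noncentrality is 0.5 × √(128 / (4 × (1 − r²))): 2.83 at r = 0, 2.97 at r = 0.3 and 3.27 at r = 0.5. The corresponding powers are 80.1%, 83.7% and 90.0%, in line with the simulation.

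**6. Precision with lecturers as the units.** Section 6.2 has "expected study drop-out of about 20%, 150 participants must be included in the study", which leaves 150 × 0.8 = 120 completers, or 20 per lecturer. With three lecturers per arm and 4 degrees of freedom, the variance of the difference is (2/3) × [ICC + (1 − ICC)(1 − r²)/20], if the covariate explains only variation within lecturers.

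| ICC | No extra covariate | r = 0.3 | r = 0.5 |
|---|---|---|---|
| 0.02 | 42.9% | 45.1% | 49.8% |
| 0.05 | 32.6% | 33.7% | 36.1% |

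The gain from fixed adjustment is then about 1 to 2 points at r = 0.3 and about 4 to 7 points at r = 0.5. This is measured against no extra covariate, so it is roughly the most the rule could forgo.

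**7. Type I error.** In the individually randomised simulation with no effect, the rule rejects 5.1%, 4.4% and 4.2% of the time at r = 0.2, 0.3 and 0.5.

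**The case against.** The strongest reply is that the protocol already fixes the covariate that usually matters most. That stands. A reader might infer from the conditional sentence that all baseline adjustment is left to chance, but the mixed models carry pre-test data in any case. The rule governs additional covariates only, and the power figures have to be read that way.

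The flag rates are conditional as well. Section 6.1 says the university system allocates students to lecturers at random. Before any teaching, the pre-test ICC could then be near zero and the flag rate near 5%. A reader might infer that the screen is bound to over-reject here, but the protocol gives no figure to support that.

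A reader might also infer that the rule inflates type I error. The simulation shows no such effect, and the screen looks only at pre-test data.

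It can further be said that some response to imbalance is needed. Section 6.6 has lecturers invite their own students, and the timeline in Section 11 puts lecturer training before student recruitment, so imbalance may reflect who was recruited as well as chance. The need is real. A significance test is a poor guide to either kind of imbalance, and a sensitivity analysis can meet the need without making the main model conditional.

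Finally, Section 5 separates "1) students who are required to enrol in the physical education course; 2) students who choose to enrol in the physical education course", and enrolment type might look like the obvious covariate to fix. The protocol does not say that it predicts any outcome. The Synopsis and Section 6.1 describe an elective unit, so it may hardly vary among participants.

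**Conclusion.** The point holds at moderate weight: the rule should be changed, but it does not invalidate the trial. Section 6.3 makes the choice of additional covariates depend on an observed between-arm p-value, which is the wrong criterion. Predictors that Section 3 names will usually be left out of the physical activity model.

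The precision lost concerns predictors other than the outcome's own pre-test value. It is small if their residual correlation is 0.2 to 0.3 and larger only if it is near 0.5. Both are assumptions, and clustering by lecturer, which limits power far more than this rule does, shrinks the loss further. The excess flagging depends on assumed pre-test ICCs and vanishes if these are near zero. That the main model is not fixed in advance depends on none of these assumptions.

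**What to change.** In Section 6.3:
- Delete the between-arm significance tests at pre-test and the sentence that adjusts for significant differences.
- Keep each outcome's own pre-test score in its model, and say so explicitly.
- Name in advance a short list of student-level covariates that are already collected, and include them whatever the observed balance. For physical activity these would be pre-test knowledge and one prespecified BREQ-2 motivation score.
- Show pre-test values by arm descriptively.
- Report any analysis adjusted for further observed imbalance as a sensitivity analysis only.

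The cost is a few sentences of text and a few student-level degrees of freedom. No new measurement is needed. Lecturer- or class-level covariates should be avoided, because six lecturers leave only 4 degrees of freedom for the comparison between arms.

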| INTERVENTION/S         | A 16-week physical education course incorporating the modified prototype Learning Management System (LMS) and mobile app.                                                                                                                                                                                                                                                                                                                                                                                                                                                                                                                                                                                                                                                                      |
| NUMBER OF PARTICIPANTS | 6 lecturers (a) n=3 will be assigned to the intervention group, (b) n=3 will be assigned to the control group.
n=300 students will be randomised 1:1 to either an intervention arm (a) n=150 a technology-supported physical education group or (b) n=150 usual physical education.                                                                                                                                                                                                                                                                                                                                                                                                                                                                                                        |

|                                |                                                                                                                                                                                                                                                                                                  |
|--------------------------------|--------------------------------------------------------------------------------------------------------------------------------------------------------------------------------------------------------------------------------------------------------------------------------------------------|

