## 6. RESEARCH PLAN / STUDY DESIGN

### 6.1 Type of study

This is a two-arm parallel, randomised controlled trial of a technology-supported physical education course intervention for students enrolled in an elective unit of study. The six lecturers who agree to participate will be randomly assigned to the intervention or control group. Students who enrol randomly by the University system with the participated lecturers of physical education course will be invited to participate in the study. The intervention lecturers will have lecturer training and implement the 16-week technology-supported physical education course intervention for one semester. The Primary outcome is to examine the difference in students' physical activity levels, knowledge and motivation at post-test (at the completion of a 16-week semester) compared with the control group. The secondary outcome is students' experience and enjoyment of the technology-supported physical education course intervention.

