#### **6.4 Recruitment and selection of participants\***

The randomised controlled trial will include six lecturers and six classes (20 to 50 students each class or  $n=300$ ). There are two recruitment processes in this RCT including the lecturer and students. The lecturer will be included in the RCT if he/she meets the following inclusion criteria: 1) run two classes of the physical education course; 2) willing to take part in lecturer training before the physical education course class begins; and 3) willing to invite their students to take part in the pilot study. The chief investigator A/[name] will be sending the recruitment to applicable members of staff at Universitas Pendidikan Indonesia especially lecturers who run the elective physical education course.

The chief investigator A/[name] will be sending the recruitment letter to students enrolled in a physical education course via the participating lecturers (and consenting). Participation in this RCT is voluntary, and all participants will be given Participant Information Statements and invited to sign a Participant Consent Form to participate. Participation or non-participation in this study will not affect students' scores in physical education courses. The number of students in each class varies from 20-50 students. Students will be included in the RCT if they meet the following inclusion criteria: 1) students enrolled in a physical education course with a lecturer who will participate in the pilot study; 2) voluntarily participate in the RCT; and 3) owns an android smartphone. The six lecturers who agree to participate will be randomly assigned to intervention or control. Participation in this RCT is voluntary, and all lecturers and students will be given Participant Information Statements and be invited to sign a Participant Consent Form to participate.

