## 6.6 Intervention

The six lecturers who agree to participate will be randomly assigned to intervention or control and will be asked to invite the students who enrol in their physical education course. The intervention lecturer will have lecturer training and implement the technology-supported physical education course for one semester (16 weeks). The outcome will be assessed at pre-test (1st week of physical education course after students agree to participate) and post-test (last week of the physical education course). Students will also be invited to participate in a focus group about their experience using the technology at the end of the course. The intervention group will receive 16 weeks of the physical education course incorporated with a modified prototype.

The type of technology that will be utilised in the RCT is a lecturer site and a student's mobile app that incorporated the physical education course at a university setting. The lecturers' website is entitled PESSPA (Physical Education Supporting Site for Physical Activity), while the student's app is entitled PESAPA (Physical Education Supporting App for Physical Activity). The PESSPA includes the following features (1) Learning management system features such as uploading course materials (text, pdf, picture, video, direct link), creating quizzes, creating assignments, creating discussions for every lesson week (2). Reviewing students goal settings, physical fitness test results, dietary and physical activity records; and (3). Uploading exercise examples and exercise video guidelines. The PESAPA includes the following features: (1) Access course materials (informative texts, pdfs, pictures, videos, etc.), quizzes, assignments submission, and weekly discussions; (2) goal settings opportunities, physical fitness testing protocols, dietary and physical activity recording opportunities; and (3). Access exercise examples and exercise video guidelines.

Figure 1 shows the screenshot of the PESSPA where lecturers are able to manage their physical education course such as adding text, adding file resources, embedding file from google drive and embedding video from youtube. Course material uploaded by lecturers can be access by students via PESAPA (see Figure 2). These figures only show one of the PESSPA and PESAPA feature interpreted the initial design principle one.

[figure not shown]

Figure 1. Screenshot of learning management system features on PESSPA.

[figure not shown]

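### Lecturers are the randomised units, but the synopsis and 6.2 say students are and 6.3 names no lecturer effect; if lecturer is left out, a nominal 5% test has a true size of about 7% to 25% for assumed ICCs of 0.01 to 0.10

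*Protocol*

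**What the plan says.** **Unit of randomisation.** Protocol 6.1: "The six lecturers who agree to participate will be randomly assigned to the intervention or control group". Section 6.6 repeats this and adds how students come in: lecturers "will be randomly assigned to intervention or control and will be asked to invite the students who enrol in their physical education course". Section 6.4 also assigns the six lecturers at random. Section 6.2 gives the split as "a) n=3 will be assigned to the intervention group" and "b) n=3 will be assigned to the control group". The synopsis and 6.2 then make the student the unit: "n=300 students will be randomised 1:1 to either an intervention arm".

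**How students reach a lecturer.** Protocol 6.1: "Students who enrol randomly by the University system with the participated lecturers of physical education course will be invited to participate in the study". This describes class enrolment by the university, not allocation to an arm.

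**Sample size (6.2).** d = 0.5, two-sided alpha 0.05 and 80% power give 128 students. This becomes 150 for about 20% drop-out and 300 invited for a 50% response. No ICC or design effect is mentioned.

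**Analysis (6.3).** Arms are compared at pre-test with independent-samples t-tests or Mann–Whitney tests, and variables that differ significantly are adjusted for in the main analyses. For the main analysis, "Linear mixed models will be used to analyse the differential change between groups on all outcomes from pre-test to post-test", with pre-test as covariate. The only reason given for a mixed model is its handling of missing data. Lecturer and class do not appear in the section.

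**The concern.** Students taught by one lecturer for 16 weeks share that lecturer's skill and enthusiasm and the course of that class. With three lecturers per arm, the arms can differ at post-test for these reasons alone. The knowledge outcome is particularly exposed, because section 9.1 builds the quiz on the course's own learning outcomes.

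The difference in lecturer means between arms enters the estimated effect under any model. What the model decides is whether the standard error allows for it. A student-level model moves lecturer variation within each arm into the residual and divides by the number of students. The interval is then too narrow and p-values are too small.

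Nothing in the text leads the analyst to the lecturer. The synopsis and 6.2 call students the randomised units, the sample size treats them as independent, the pre-test comparisons do the same, and the mixed model is justified on other grounds. At stake are the type I error of every between-arm comparison and the truth of the 80% power claim.

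**Working it through.** **1. Reproduce the plan's figure.** For independent students, n per arm = 2(1.960 + 0.842)²/0.5² = 62.8, so 63 by the normal approximation. The noncentral t gives 64 per arm, 128 in total. The stated 128 is therefore exactly the figure for individually randomised students, with no allowance for clustering.

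**2. Inputs for the check.**
- Clusters: 6 lecturers, 3 per arm (6.1, 6.2).
- Analysed students: 150 × (1 − 0.20) = 120 (6.2), so m = 120/6 = 20 per lecturer.
- ICC: not in the protocol. Assumed range 0.01 to 0.10, with 0 for reference.

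**3. True size of a nominal 5% test that ignores lecturer.** Design effect DE = 1 + (m − 1) × ICC; size = 2 × [1 − Φ(1.96/√DE)].

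| ICC | DE | 1.96/√DE | True size |
|---|---|---|---|
| 0 | 1.00 | 1.960 | 5.0% |
| 0.01 | 1.19 | 1.797 | 7.2% |
| 0.02 | 1.38 | 1.668 | 9.5% |
| 0.05 | 1.95 | 1.404 | 16.0% |
| 0.10 | 2.90 | 1.151 | 25.0% |

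Simulation under no effect agrees. A student-level model with pre-test as covariate rejected in 7.3%, 16.5% and 26.0% of trials at ICC 0.01, 0.05 and 0.10. A t-test on the six lecturer means (4 df) rejected in 5.0%, 5.0% and 4.7%.

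**4. Sensitivity to class size.** Over ICC 0.01 to 0.10, the size runs from 7.8% to 28.8% at m = 25. At m = 40 it runs from 9.6% to 37.6%; that is the case if all 300 students enrolled and 20% dropped out (240/6). Taking m = 20 is the milder reading of 6.2.

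**5. Power of the valid analysis.** Lecturer-level test on 6 − 2 = 4 df, critical t = 2.776, noncentrality = 0.5 × √(60/(2 × DE)) with 60 students per arm.

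| ICC | Noncentrality | Power, 120 students | Power, 300 students (m = 50) |
|---|---|---|---|
| 0 | 2.74 | 55% | 89% |
| 0.01 | 2.51 | 48% | about 75% |
| 0.05 | 1.96 | 33% | 43% |
| 0.10 | 1.61 | 24% | 28% |

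Like the plan's own 128, these figures credit no gain from the pre-test covariate. More students per class help little once the ICC is appreciable, because the number of lecturers sets the limit. At m = 20, 80% power would need about 5, 8 or 11 lecturers per arm at ICC 0.01, 0.05 or 0.10.

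**6. Limit set by six clusters.** There are C(6,3) = 20 ways to choose three of six lecturers, so the smallest two-sided randomisation p-value is 2/20 = 0.10. The protocol proposes no such test, so this is not an error in 6.3. It does mean that any p < 0.05 rests on the model.

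**The case against.** The strongest reply is that 6.3 specifies linear mixed models without listing their random effects, and such detail is commonly left to the SAP, which is not at hand. The design even hints at a cluster effect. There is one pre-test and one post-test, so with pre-test as covariate each student contributes a single outcome value, and a student random effect could not be separated from residual error. A lecturer or class effect would then be the natural reason for a mixed model. This stands as far as the main model goes: omission of lecturer is an inference, because the text neither includes nor excludes it. It does not reach what the protocol does fix, namely the wrong unit of randomisation in the synopsis and 6.2, an independent-student sample size, and independent-samples tests at pre-test that feed into the adjustment. An SAP faithful to this text could carry the error forward.

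A reader might infer that the trial's 5% test simply is a 7% to 25% test. The documents do not support that. The range needs lecturer to be omitted and an ICC that the protocol does not give. University enrolment described as random, and identical course content in both arms, may favour the lower part of the range. Neither removes lecturer effects that arise during 16 weeks of teaching.

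A reader might also infer that a lecturer term would remove lecturer differences from the estimated effect. It would not: with equal class sizes the estimate is the same, and only its standard error and degrees of freedom change.

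**Conclusion.** The concern holds in conditional form. It is certain that the protocol contradicts itself on the unit of randomisation, and that its sample size and pre-test comparisons treat students as independent. That the main model will do so is likely on the wording but not stated. If lecturer is not modelled, the standard error is too small and the true size of a nominal 5% test is about 7% to 25%, assuming ICCs of 0.01 to 0.10 and about 20 analysed students per lecturer; at ICC 0 it is 5%. If lecturer is modelled properly, the size is held near 5%, but the 80% power in 6.2 is not delivered: it is about 48%, 33% and 24% at ICC 0.01, 0.05 and 0.10 with 120 students. So either the test or the stated power fails, and correcting 6.3 alone is not enough.

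**What to change.** 1. State in the synopsis, 6.2 and 6.3 that the lecturer is the unit of randomisation, and remove the statement that students are randomised.
2. Require in 6.3 a random intercept for lecturer in every between-arm model, with Satterthwaite or Kenward-Roger degrees of freedom. Add class within lecturer if two classes are used: 6.4 requires lecturers to run two classes but counts six classes in all, and 6.5 allows a further class to be invited.
3. Report the analysis of the six lecturer means on 4 df as a check. It matters here because with so few clusters the lecturer variance is often estimated as zero. For balanced classes of 20 the chance that the between-lecturer mean square does not exceed the within-lecturer one, P(F with 4 and 114 df < 1/DE), is about 50% at ICC 0.01 and 15% at 0.10.
4. Report the ICC, and lead with the estimate and its confidence interval.
5. Restate the power in 6.2 for six lecturers over a stated ICC range.

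The cost is wider intervals and a less favourable stated power. The changes are to wording and analysis only and need no new data. They should be settled before outcomes are seen, because the choice of model can decide significance.

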## 9. OUTCOMES

### 9.1 Primary outcome

Difference in physical activity levels, knowledge and motivation at 16 weeks' time point compared to physical activity levels measures at baseline.

Three outcomes were measured in the pre-and post-intervention. First, The International Physical Activity Questionnaire-Short Form (IPAQ) was used to measure the student's physical activity levels. IPAQ is internationally recognised as a valid and reliable questionnaire for measuring physical activity levels. The IPAQ is publicly available, it is open access, and no permissions are required to use it. The IPAQ is suitable for adults between 15 and 69 years of age and is primarily used for population surveillance of physical activity levels. The IPAQ short form records the activity of four intensity levels: 1) vigorous-intensity activity such as aerobics, 2) moderate-intensity activity such as leisure cycling, 3) walking, and 4) sitting. Then, to measure student's motivation, the Behavioural Regulation Exercise Questionnaire (BREQ-2) was used which has 19 questions using a 5-point Likert scale for responses. BREQ-2 is a valid and reliable measure five subscales of physical activity motivation: Amotivation, External Regulation, Introjected Regulation, Identified Regulation, and Intrinsic Regulation within university students population. Lastly, to measure physical activity knowledge, we developed physical activity knowledge quizzes consisting of 20 multiple choices question based-on the learning outcome of the physical education course. To demonstrate construct validity, two physical education experts reviewed the quizzes whether the questions were

aligned with the learning outcomes. Then, test-retest reliability was performed to measure the consistency of the quizzes with 20 university students within two weeks. The coefficient correlation between test and retest was high  $r=0.833$  ( $P < 0.05$ ).

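### The mixed model is justified by robustness to missing-data bias, but with one post-test and the pre-test as covariate it is a complete-case ANCOVA and adds no protection beyond that

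*Protocol*

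**What the plan says.** Section 6.3 (Statistical analyses) sets the main analysis: "Linear mixed models will be used to analyse the differential change between groups on all outcomes from pre-test to post-test", and it does so "using pre-test data as the covariate". The reason given is "Linear mixed models will be used because these models are robust enough to withstand the biases from missing data". The section names no condition under which this holds.

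There are two measurement occasions. Section 6.6 (Intervention) has "The outcome will be assessed at pre-test (1st week of physical education course after students agree to participate) and post-test", the latter in the last week of the course. Section 9.1 (Primary outcome) agrees: "Three outcomes were measured in the pre-and post-intervention". No intermediate outcome measurement is described.

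Section 6.2 (Sample size) expects appreciable loss: "Taking into account an expected study drop-out of about 20%, 150 participants must be included in the study".

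Section 6.3 also plans to compare the pre-test values of completers with those of students lost to follow-up. Its adjustment rule, as worded, concerns variables that differ between groups.

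**The concern.** A mixed model can draw on incomplete students when they have other outcome rows in the model, such as intermediate visits. Here there are none. With the pre-test on the right-hand side, the only outcome row is the post-test, and a student who lacks it leaves the analysis. The property given as the reason for choosing the model is then not one that the mixed model supplies.

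The risk is that a report cites the model choice as its missing-data safeguard. Participation is voluntary and the outcomes are an online questionnaire and a quiz, so loss related to how a student fared is conceivable, although the documents give no reasons for drop-out and no split by arm. If it occurs in one arm, the effect on the primary outcome is biased and nothing in the model corrects it.

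**Working it through.** **1. The plan's own figures.** Section 6.2 uses d = 0.5, two-sided alpha 0.05 and 80% power with 1:1 allocation. A two-sample t-test needs 63.8, so 64 per arm, or 128 in total. The stated 128 reproduces. A 20% loss from 150 is 150 × 0.20 = 30 students, leaving 120 with a post-test.

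**2. What the model uses.** Taken as a post-test model, it is

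post = a + b·arm + c·pre + (any class or lecturer effect) + error,

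with one row per student. A missing post-test means no row, and so no contribution to b. A class or lecturer effect changes how completers are weighted but does not bring lost students back.

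**3. Numerical check.** One data set of 150 students was simulated with about 20% of post-tests missing at random; 30 were missing.
- Mixed model with a class random intercept, given all 150 students: 120 rows used, arm effect 0.265145 (SE 0.1636).
- Ordinary ANCOVA on the 120 completers: arm effect 0.265145 (SE 0.1632).

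The class variance was estimated at about zero, which is why the two agree so closely. The general point is the row count: the 30 lost students added nothing.

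**4. Bias under three mechanisms.** Assumptions: 1,000 runs of 1,000 students, true effect 0.50 SD, pre-post correlation 0.5, drop-out 20% to 21% in each arm. In the second and third rows, the log-odds of loss in the app arm fall by 1.0 per SD of the pre-test or post-test respectively. Loss in the control arm is random.

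| Drop-out depends on | Pre-test as covariate (complete-case ANCOVA) | Both times as outcomes, all rows |
|---|---|---|
| nothing | 0.499 | 0.499 |
| pre-test, app arm | 0.498 | 0.499 |
| unseen post-test, app arm | 0.634 | 0.636 |

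In the last row the covariate model is off by 0.634 − 0.50 = 0.134 SD, and 0.134 / 0.50 = 27% of the assumed effect.

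**5. A simpler illustration.** Suppose app-arm completers gain 0.50 SD over control, 20% of the app arm is lost, and those lost would have gained a fraction f of that. The effect in all enrolled is 0.8 × 0.50 + 0.2 × f × 0.50 = 0.40 + 0.10f, while the completers show 0.50.
- f = 0: 0.40, overstated by 0.50 / 0.40 − 1 = 25%.
- f = 0.5: 0.45, overstated by 11%.
- f = 1: 0.50, no bias.

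**6. What the planned comparison can show.** Comparing pre-test values can reveal that those lost started lower. It cannot show whether, among students with the same pre-test, those lost ended lower. The third row of the table turns on that second question.

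**The case against.** The strongest reply is that the model is sound and only one sentence is too strong. Much of this stands. A reader might infer that the analysis has no protection at all. It does have some: when drop-out depends only on arm and pre-test, the covariate model is unbiased (0.498), whereas a complete-case change score gives 0.409. That protection comes from the covariate, and plain ANCOVA has it equally.

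A reader might also infer that treating the pre-test as an outcome would cure the problem. It would not: 0.636 against 0.634 when loss depends on the post-test. A constrained longitudinal model mainly helps to retain students with a missing pre-test.

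A third tempting inference is that the pre-test sits on both sides of the model, because the text speaks of change "from pre-test to post-test, using pre-test data as the covariate". If both times were outcomes and the pre-test also a covariate, simulated false-positive rates are about 7.7%, 6.7% and 6.2% at assumed pre-post correlations of 0.3, 0.5 and 0.7 (120 students, no clustering, student variance at zero). A covariance structure that allows negative within-student correlation brings them back to 5.0%, 5.2% and 5.1%. The protocol does not state such a model, and sections 2 and 6.1 describe the primary outcome as a group difference at post-test, which fits ordinary ANCOVA. The ambiguity is a reason to write down one model, not evidence of an inflated error rate.

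It is also fair that a drop-out comparison is planned, and that a sensitivity analysis and a named missing-data assumption may be left to a statistical analysis plan. Their absence is not the fault here. The fault is a stated justification that is untrue without a condition.

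**Conclusion.** The concern holds in a limited form. As specified, the main analysis is a complete-case ANCOVA, possibly with a class or lecturer effect. The mixed model adds nothing to ANCOVA against missing data, and the unconditional robustness claim is wrong. Validity requires that drop-out depend on nothing beyond arm, pre-test and the included covariates.

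At the expected 20% loss, the illustrations range from no bias to an overstatement of about 25% to 27% of the effect. They rest on assumed mechanisms, an assumed correlation of 0.5 and loss tied to outcome in the app arm only. They are not forecasts for this trial, and poor-outcome loss concentrated in the control arm would push the estimate the other way. The documents do not show that drop-out will be of this kind; they also give no ground for saying that the model would withstand it.

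**What to change.** - Replace the robustness sentence in section 6.3 with its condition: the estimate is unbiased if post-tests are missing at random given arm, pre-test and the included covariates.
- State one model: post-test on arm, with the pre-test as covariate and a random effect for the randomised lecturer, so that the pre-test is never both outcome and covariate.
- Include pre-test variables that predict drop-out, whether or not they differ between arms.
- Add a sensitivity analysis that shifts the missing app-arm post-tests down to no benefit, and report whether the conclusion holds.

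A constrained longitudinal model is optional; it does not reduce the bias described here. The cost is a change of wording and one extra analysis run. No new data are needed.
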